
**Inclusion Criteria:** Men and women with two or more of the five targeted chronic diseases; daily Internet access (home, work or other environment) by any means (such as personal computer, personal data assistant or smartphone); over 19 years of age; and able to read, write and understand English without difficulty.

**Exclusion Criteria:** Patients with significant co-morbidities (excluding the five targeted conditions these include HIV, uncontrolled metabolic/endocrine disorders, prior stroke or other conditions affecting cognitive abilities to

provide consent and participate, alcohol/drug addiction) that may interfere with effective management; patients who have scheduled surgical procedures; and patients who are unable to provide informed consent.

Detailed records will be kept of all individuals who are screened for the study to clearly define the population from which our study cohort will be derived and to ensure our reporting will follow the CONSORT guidelines.

**Study Outcomes:** *The primary outcome will be the difference between the iCDM and usual care groups in hospital admissions from the time of randomization to the end of two years.* Data will be collected by participant self-report and confirmed through access to participant medical records in those who sign the study's Medical Records Release Form. We will also collect data from Provincial Databases hosted by the Population Data BC; Medical Services Plan payment information file, PharmaCare file, hospital separations file and Vital Statistics deaths and clinical deaths on secondary outcomes of healthcare utilization such as length of hospital admissions, emergency room visits, physician/nurse practitioner visits, diagnostic and lab procedures. In addition, secondary outcomes will include patient quality of life, self-management, patient and provider experience, and mortality (see below).

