**Baseline Assessment:** We will collect the following data variables on all consenting participants: social demographics, medical history, current medications, self-management and quality of life, smoking status, alcohol consumption, e-health literacy, and recent diagnostic and lab tests (<6 months). The baseline (and follow-up) assessment will be conducted without the need for the research coordinator to meet with the patient. Data on patient demographics, medical history, current medications, smoking status, and recent diagnostic and lab tests will be abstracted from the patient's physician's/nurse practitioner's medical record and confirmed by telephone with the patient. For all other outcomes we will be using self-administered questionnaires which will be mailed to the patient with a stamped return envelope to mail back. If after two weeks the questionnaires have not been received, the research coordinator will contact the patient by telephone to follow-up. We will create a toll-free number for participants to call the research coordinator to return any messages from the coordinator and ask questions regarding assessment data collection so that participants will not have to incur long-distance phone charges.

**Randomization:** Participants will be stratified by sex and site of recruitment (based on health authority), and then randomized to either usual care or the iCDM using computer-generated variable blocks of 2, 4 and 6 within a web-based randomization system. A research assistant not involved in data collection will access the randomization system using a unique authorization code. The date and time, patient identifiers and randomization codes will automatically be maintained in a transaction file. This same research assistant will be responsible for communicating group assignments to the study participants. Participants will be informed not to discuss their group assignment with the research coordinator responsible for data collection to ensure the study

remains single-blinded. If at the time of being informed of their group assignment, the participant becomes distressed, anxious or upset, the research coordinator will inform the participant that the study psychologist is available to discuss their concerns if they wish.

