**Usual Care Group:** Participants randomized to usual care will be given educational information regarding general chronic disease management and a list of Internet-based resources. There are no formal specialized ambulatory care clinics in the areas in which our target participants reside. Therefore, the overwhelming majority of patients are managed exclusively by their family physician. In some cases, patients may be referred to a local internist and may also have the opportunity to contact local community nurses for guidance on their care. Participants in the usual care group will be free to seek treatment as they wish and as their clinical providers see appropriate. There will be no contact between the study personnel and the usual care participants for the duration of the study, or any attempt to control for the level of patient care. If at the end of the study the results indicate superiority of the intervention, the participants in the usual care group will be offered the vHFC intervention for a three-month period.

**Intervention Group:** The iCDM is a nurse-supervised patient self-management and monitoring system that has been designed by a clinical advisory committee that includes specialist, family physician, allied health and patient representation (see Appendices for greater detail). The iCDM is meant to support patients and their family physicians/nurse practitioners in their care and not to supplant it.

Upon randomization, a letter will be sent to the patient's primary care provider (PCP) from the study investigators informing them of their patient's participation in the study, a brief description of the study. The iCDM nurse will contact the participant's family physician/nurse practitioner to follow-up on the letter, discuss the intervention protocol and preferred method of communication, as well as to offer them access to the iCDM to view their patient's progress. Throughout the intervention, the iCDM nurse will communicate with the participants' family physicians/nurse practitioners to work collaboratively on participant care/action plans. Care plan development and communication with family physicians/nurse practitioners will be respectful of the family physician's/nurse practitioner's time and cognizant of any existing supports put in place for such purposes.

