**Security and Privacy Issues:** The iCDM will be developed with the utmost attention to compliance with BC Privacy Legislation, security requirements of our partner health authorities. The iCDM program will be password protected and hosted on a standalone secure server. The website will be housed on a dedicated server. All data transmissions to and from the web server will be conducted via an SSL Internet connection to ensure encryption of transmitted data (similar to online banking). During the consent procedure, potential participants will be informed of their security and privacy rights as well as our efforts to ensure that these are maintained.

**Follow-up Assessments (both groups):** One year post-randomization, participants will be contacted by the research coordinator by telephone to [administer the EuroQol EQ-5D-5L questionnaire and to](#) ask simple

---

 Given our method of recruitment through physician offices and ambulatory care clinics, we anticipate our patient pool will be derived from practices where physicians will be informed and supportive of the study.

questions regarding their health in the past year to assess any adverse events. This will consist of an initial question asking the participant if they have been admitted to hospital for any reason in the previous year. If the participant answers 'yes' then additional questions on the nature and location of the event will be collected in order to report the event to the overseeing REBs (see below). If no contact has been made after a total of three unresponsive telephone calls the participant's family physician/nurse practitioner will be contacted to assess the vital status of the participant. If the physician/nurse practitioner indicates the participant is alive, we will confirm their contact details and proceed with sending a letter to the participant. If a response is not received within 10 days, the participant's alternate contact will be telephoned (this will have been collected at the time of participant consent). If the physician/nurse practitioner indicates the participant has died, we will collect the appropriate medical records for reporting the adverse event to the overseeing REBs.

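### The research coordinator, who must stay blind to group, is named as the person who responds when a participant is distressed at learning the assignment

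*Protocol*

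**What the plan says.** **Disclosure and blinding (Protocol, Randomization).** A research assistant who takes no part in data collection operates the randomization system. "This same research assistant will be responsible for communicating group assignments to the study participants". The coordinator is kept out of this step: "Participants will be informed not to discuss their group assignment with the research coordinator responsible for data collection", so that the trial stays single-blinded.

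**Response to distress (same section, next sentence).** For a participant who reacts badly on hearing the group, the rule reads: "the research coordinator will inform the participant that the study psychologist is available to discuss their concerns if they wish".

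**What the coordinator does later (Follow-up Assessments, both groups).** "One year post-randomization, participants will be contacted by the research coordinator by telephone to" administer the EQ-5D-5L and ask whether they have been admitted to hospital. At two years the coordinator contacts participants again and repeats the adverse event questions. The section ends by restricting coordinators to screening, recruitment, assessment and adverse event reporting.

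**Primary outcome (Study Outcomes).** The outcome is the difference between groups in "hospital admissions from the time of randomization to the end of two years". It is collected by self-report and confirmed in medical records for those who sign a release.

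**Usual care (Usual Care Group).** "There will be no contact between the study personnel and the usual care participants for the duration of the study". The sentence names no exception for assessments.

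**The concern.** Participants know their group, and so does the assistant who tells them. The blinding of outcome collection that the protocol describes therefore rests on the coordinator not learning the assignment. The distress rule brings that person into a conversation about the assignment, at or close to the moment of disclosure, with a participant who has been asked not to raise the subject with them.

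At stake is the neutrality of the person who asks the admission question, follows up a positive answer and takes the one-year EQ-5D-5L by telephone. A coordinator who knows or suspects the arm may probe or record differently without meaning to.

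The unqualified no-contact sentence for usual care is a separate and smaller matter. It disagrees with a follow-up section that requires contact in both groups.

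**Working it through.** No arithmetic applies. The protocol gives no rate of distress at allocation, no rate of unblinding and no figure that depends on either. The check sets the provisions side by side.

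1. **Who may know the group.** Under Randomization, the assistant may and the data-collecting coordinator may not. The assistant's separation from data collection and the instruction to participants both serve that one aim.

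2. **Who acts when disclosure causes distress.** The same paragraph names the coordinator. The trigger is the participant's reaction at the time of being told the group. To act on it, the coordinator must either be present at disclosure or hear of the reaction soon after. Both routes run against step 1.

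3. **Whether the task lies within the coordinator's role.** The closing paragraph of Follow-up Assessments lists four duties and says the role is limited to them. Responding to distress over allocation is not among them. The rule therefore conflicts with a second provision as well as with the blinding instruction.

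4. **What the coordinator can influence.**
   - Hospital admissions: asked by the coordinator at one and two years. Self-report is where collection of the primary outcome starts.
   - EQ-5D-5L: administered by telephone at one year, and intended for the cost-utility analysis.
   - Less exposed: mailed self-administered questionnaires, data abstracted from the provider's record, website use logs and provincial database records.

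5. **What protects the admission count.** Medical records confirm self-report, but only for those who sign the release. Study Outcomes mentions the provincial databases in connection with secondary utilization measures. Healthcare Utilization lists hospital admissions first and says the databases will also be accessed, without that limit. How far the databases check the primary outcome is thus open to either reading. Neither source checks an EQ-5D-5L answer.

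6. **No-contact sentence against follow-up.** Usual Care Group rules out contact throughout the study. Follow-up Assessments is headed as applying to both groups and requires coordinator calls at one and two years, with mailed questionnaires at two years. The two do not agree as worded. The follow-up section is the specific provision, and it shows what is intended.

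**The case against.** **It is probably a drafting slip.** Only the assistant is named as taking part in disclosure, and the role limits elsewhere exclude this task. Writing coordinator for assistant is an easy error. That may well be so, but it does not make the sentence harmless: staff work from the text, and the text names the wrong person. If it is a slip, the correction is the same.

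**The sentence does not unblind anyone.** A reader might infer that the coordinator is told the allocation, or is unblinded across the trial. The protocol does not support that. The coordinator's only stated act is to mention the psychologist, no sentence passes on the group, and the rule applies only to participants who become upset. What stands is a risk of unblinding in that subset.

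**The bias is not shown to differ by arm.** A reader might infer that distress is commoner among those assigned to usual care, so that unblinding is selective. That is plausible, but nothing in the protocol says so, and it must be labelled an assumption.

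**The primary outcome is well protected.** The admission item is a set yes/no question, records confirm the answer for those who sign the release, and databases are available. Participants also know their own arm, so bias from their side exists whatever the coordinator knows. This stands as a limit on the effect on admissions. It helps less with the follow-up questions after a positive answer, and not at all with the telephone EQ-5D-5L.

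**The no-contact sentence concerns care.** It stands in a description of usual care and goes on to disclaim any control over the level of care. This largely stands. A reader might infer that the sentence, taken literally, removes outcome data for the whole control arm (318 / 2 = 159 if allocation is equal). It does not: follow-up is expressly required in both groups, and record abstraction and database access do not depend on contact with the participant.

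**Conclusion.** The point holds as an internal conflict in an operative rule. The Randomization section protects the coordinator's blinding and then assigns the coordinator a task that puts it at risk. The role limits under Follow-up Assessments point the same way.

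The size cannot be computed from the protocol. The exposure is limited to participants distressed at allocation, whose number is unknown and may be small. For admissions, record confirmation and the databases reduce the consequence. For the one-year EQ-5D-5L, no such check is described. The conclusion assumes only that staff follow the sentence as written. It does not need the assumption that distress differs between arms; a claim of bias in a particular direction would.

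The change is worth making because it removes an avoidable threat to blinding at no cost. The no-contact sentence is a minor wording conflict that the follow-up section already resolves.

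**What to change.** - **Randomization.** In the distress sentence, replace the research coordinator with the research assistant who discloses the assignment. That person already knows the group and collects no outcome data. Leave the psychologist offer itself unchanged.
- **Usual Care Group.** Add to the no-contact sentence the exception *apart from the scheduled one- and two-year assessments*, so that it agrees with Follow-up Assessments (both groups).
- **Optional.** Have the coordinator note at each call whether the group was revealed or suspected. This is good practice, and its absence from the protocol is not an error.

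The cost is two wording changes, plus one form field if the optional item is adopted. No staff are added, and sample size, power and analysis do not change.

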## **METHODOLOGY OF STUDY OUTCOMES AND MEASURES**

**Healthcare Utilization:** Data (hospital admissions, length of hospital stay, emergency room visits, physician/nurse practitioner visits, diagnostic and lab procedures) will be collected by participant self-report and confirmed through access to participant medical records in those who sign the study's Medical Records Release Form. We will also access provincial ministry databases at Population Data BC. *Mortality* will be assessed by accessing the Population Data BC database. We will also assess the amount of time the iCDM health professionals engage with the program and the participants so that we will be able to estimate patient loads that can be managed for future implementation.

**Psychometric Measures:** *Quality of Life* will be assessed by the Medical Outcomes Study 36-item Short Form survey. This is a widely-used, self-administered instrument that provides indices of various components of the construct of "quality of life": patient health, patient ability to perform certain tasks and any adjustments they had to make. *Self-management* will be assessed by the Health Education Impact Questionnaire (heiQ) which is used for assessing patient education and self-management in participants with chronic conditions. *Social support* will be assessed using the Medical Outcomes Study Social Support Scale in which participants report their level of perceived support. [The EuroQol EQ-5D-5L health questionnaire will be used to assess health outcomes. We will use data collected from it to perform a cost-utility analysis that takes into account benefits experienced by study participants.](#)

**Patient and Provider Experience and Satisfaction:** Participants enrolled in the iCDM intervention will undergo a semi-structured, open-ended interview at the end of the intervention to explore patient experiences and to increase our understanding of patient factors that influence acceptance and use. These interviews will be transcribed and entered into the qualitative research software NVivo 7 (QRS International, Victoria, Australia) which will be used to manage data and to provide a structure for analysis. A three-stage analysis of the transcript data (open-coding, axial coding, and selective coding) will be guided by an inductive iterative approach. Participants for the interview will be identified by stratified purposeful sampling with representation from both sexes and include participants from each recruitment method. The final number of interviews will be driven by the prospective discovery of factors (or concepts) that may affect participant satisfaction with care provided through iCDM. Interview transcripts will have personal identifiers removed and a double coding system will be used to link the data with the interviewee. In a similar fashion, we will interview family physicians/nurse practitioners of iCDM participants to explore PCP experience including satisfaction, attitudes and feedback. Participating physicians/nurse practitioners will be reimbursed for their time to ensure participation. Together, these interviews will help to elicit understanding of the role and meaning of the iCDM within the management these participants.

**Adherence to the iCDM** will be assessed through website use (logins) and completion of data entry. We will track which areas of the iCDM are frequented by the participants so that we can better understand which elements of the iCDM were most beneficial to participants. We will also assess the number and nature of alerts

generated per patient to provide insight into areas where participants need further support with managing their condition.

**Additional Variables Assessed at Baseline:** *e-Health Literacy* will be assessed using the eHealth Literacy Scale (eHEALS) in all participants during their baseline assessment only. The eHEALS is used to assess the combined knowledge, comfort, and perceived skills at finding, evaluating, and applying electronic health information to health problems. *Depression* will be assessed using the Center for Epidemiologic Studies Depression scale. These data will be used as potential independent determinants to identify what patient characteristics are associated with improved outcomes.

## STATISTICAL ANALYSES

We anticipate that 10% of the study population will be lost-to-follow-up at the end of study. Lost-to-follow-up will be defined as those participants who have died, withdrawn from the study or moved out of the province. Every effort will be made to obtain final data on the primary and secondary outcomes from subjects regardless of the extent of study participation to that point. *Lack of compliance to the iCDM will not be a reason for withdrawal from the study.* We will explore differences in baseline variables between those lost-to-follow-up and those who remain in the study.

The primary outcome of hospital admissions between the two groups from baseline to two (dependent variable) years will be modeled using ordered logistic regression with group assignment, age and sex as *a priori* covariates. In the event of potentially clinically relevant differences in baseline factors, we will include these covariates in the model (such as socio-demographics, e-health literacy, depression, and other morbidities). Non-normally distributed continuous variables will be transformed prior to analyses. Residual plots for the primary outcome models will be plotted and assessed for model adequacy. Secondary outcomes between the two groups will be compared using the Pearson Chi-square test for categorical variables and independent samples t-test for continuous variables. All analyses will be governed by intent-to-treat with no group crossovers.

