**Study Population:** We will recruit patients through primary care networks and other practicing primary care physicians and nurse practitioners. Physicians and nurse practitioners will be approached in Fraser Health, ~~(through Chilliwack Division of Family Practice)~~, Northern Health, Interior Health, ~~and~~ Vancouver Coastal Health ~~and Vancouver Island Health~~ who practice outside of major urban areas. These areas have been identified based on the lack of access for patients to specialized chronic disease outpatient programs. We will approach these physicians and nurse practitioners by first sending a letter to the physician/nurse practitioner briefly outlining the study and asking for their support in recruiting patients from their practice. This letter will be jointly sent from [name] and one of the physician leaders in the area (see attached letter). Many of physicians and nurse practitioners we will be approaching have electronic medical records (EMR). In those cases, we will ask the physician/nurse practitioner or another individual who has approved access to the EMR to identify potentially eligible patients (based on the disease and age criteria listed below). Physicians and nurse practitioners who do not respond to the initial letter within 10 days of the letter being sent will be sent a follow-up email from the physician leader with an electronic version of the letter and indicating that the local research coordinator will contact them by telephone to follow-up with any questions/clarifications about the study. For physicians and nurse practitioners in Interior Health, Northern Health ~~and~~ Vancouver Coastal Health ~~and Vancouver Island Health~~ who agree to support recruitment of their patients, we will draft a letter for the physician/nurse practitioner to send to those potentially eligible patients inviting them to participate in the study by contacting the study coordinator (see attached letter IH/NH/VCH, ~~VIH~~). The letter will be sent by the physician/nurse practitioner and include a copy of the patient consent form. Once the patient has contacted the research coordinator, he/she will be screened further for study eligibility and have the opportunity to ask questions regarding the study. The research coordinator will explain the consent form and obtain informed consent (this method has already received approval from the Northern Health Authority, Interior Health Authority and Vancouver Coastal Health Authority REBs). For physicians and nurse practitioners in Fraser Health who agree to support recruitment of their patients, we will draft a letter for the physician/nurse practitioner to send to those potentially eligible patients informing them briefly of the study and asking the patient for consent for the family physician/nurse practitioner to release their contact information to the research coordinator (see attached letter for release of contact information). For those patients who consent to have their contact information released to the research coordinator, the research coordinator will mail a letter of invite for the study along with the consent form (see attached letter of invite). After 10 days of the letter being mailed, the research coordinator will telephone the patient to address any questions they may have regarding the study. In addition, we will also place study brochures and posters in the physicians'/nurse practitioners' offices that can be handed out by the physician/nurse practitioner or their office assistant directing interested patients to contact the study coordinator (see attached brochure/poster). Physicians/nurse practitioners and their offices will be compensated for their time in supporting recruitment of their patients (ie: screening of their patients, sending out letters, etc.). There will be no costs to the patients to participate in this study.

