**Sample Size Determination:** We have identified a convenience sample of 318 participants as feasible based on our methods of recruitment and study timelines. Based on our current study of a 'virtual cardiac rehabilitation program' in Northern BC which has a reported drop-out rate of 12%, we have set a drop-out rate of 15% due to patient withdrawal, death and moving outside of the province, and will therefore finish with 270 participants. We will collect detailed information on the subjects who withdraw and their reasons for withdrawing. In our pilot combined clinic at St. Paul's Hospital for patients with two or more of cardiovascular disease, diabetes and chronic kidney disease, we observed 32 hospitalizations over a two-year period in the 30 usual care patients (a baseline event rate of 107%) compared to 24 hospitalizations over a two-year period in 34 patients in the combined pilot clinic (event rate of 71%) resulting in a 33.6% reduction in events. We have based the current study power estimates on a 25% reduction in hospital admissions by the iCDM. We have chosen a more conservative effect of the iCDM as the iCDM is directed more at supporting patient self-management and monitoring, and does not involve direct medical management. Based on a 25% reduction in hospital admissions, and an alpha of 0.05, we have outlined the power given the following estimated event rates using the method of Demidenko E in the table below. We have provided a range of event rates as we do not have documented event rates from our targeted patient population. If the event rate is similar to that observed in our pilot clinic at St. Paul's Hospital, we will have sufficient baseline events for a power greater than 0.80 to detect an effect of 25% reduction in events.

| Usual Care* | iCDM* | Power |
|--------------------|--------------|--------------|
| 40%                | 30%          | 0.39         |
| 50%                | 38%          | 0.55         |
| 60%                | 45%          | 0.67         |
| 70%                | 53%          | 0.78         |

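### Health authority is a stratification factor but is not in the primary model, which costs some power if admissions differ between authorities

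*Protocol*

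**What the plan says.** In the Randomization paragraph of the Research Program section, "Participants will be stratified by sex and site of recruitment (based on health authority), and then randomized" to usual care or the iCDM, using "computer-generated variable blocks of 2, 4 and 6 within a web-based randomization system".

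Under Statistical Analyses, two-year hospital admissions "will be modeled using ordered logistic regression with group assignment, age and sex as" a priori covariates. Health authority is not listed. The only route for further terms is this: "In the event of potentially clinically relevant differences in baseline factors, we will include these covariates in the model". The examples given there are social and demographic factors, e-health literacy, depression and other illness; site of recruitment is not among them. Nothing else in the protocol adds health authority to the primary model or explains its absence.

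On size, the protocol says "We have identified a convenience sample of 318 participants as feasible". On drop-out, it says "we have set a drop-out rate of 15% due to patient withdrawal, death and moving outside of the province, and will therefore finish with 270".

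**The concern.** A factor used to restrict the randomisation normally belongs in the primary analysis. Stratified blocking removes between-authority differences from the comparison of the arms, so the treatment estimate varies less from trial to trial. A model without authority does not know this, and its standard error is set as if the allocation had been unrestricted. In a logistic-type model there is a second effect: leaving out a balanced covariate that predicts the outcome pulls the treatment log odds ratio toward zero. Both effects make the test conservative and reduce power.

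Power is limited here. The sample is one of convenience, and every row of the protocol's power table is below 0.80 (0.39 to 0.78). The protocol expects more than 0.80 only if the event rate resembles that of its pilot clinic. The choice to stratify on health authority suggests that the planners thought it might matter. Recruitment also differs by authority: in Fraser Health patients first agree to release of their contact details and are then mailed and telephoned, whereas elsewhere they contact the coordinator themselves. Case mix could therefore differ.

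**Working it through.** **1. Design against model.**

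| Factor | Stratified on | A priori covariate |
|---|---|---|
| Sex | yes | yes |
| Health authority | yes | no |
| Age | no | yes |

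The baseline-difference clause does not close the gap. It is triggered by imbalance between arms, which blocking within authority is designed to prevent.

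**2. Inputs.** From the protocol: 318 randomised and 15% drop-out, so 318 × 0.85 = 270.3, or 270; blocks of 2, 4 and 6; ordered logistic regression on group, age and sex; alpha 0.05 (two-sided assumed); a 25% reduction. Assumed: 1:1 allocation (inferred from the even block sizes), four authorities, and the size of the differences between authorities, which no section gives.

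The protocol has no figure of its own for this point. Its power table involves no stratum, so nothing below rests on it. With 135 per arm, a pooled two-proportion formula gives 0.406, 0.544 (using 37.5%), 0.696 and 0.822, against the printed 0.39, 0.55, 0.67 and 0.78.

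**3. Mechanism.** Trials of 270 patients were simulated with a four-level ordered outcome and stratified blocks (2,500 to 3,000 runs per setting). Each was fitted twice:

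- planned: logit P(Y > k) = a_k + b·group + c·age + d·sex
- with site: the same plus authority indicators

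Under no treatment effect, the planned model gave:

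| Site SD (log odds) | Mean model SE | True SD of estimate | Type I error, planned | Type I error, with site |
|---|---|---|---|---|
| 0 | 0.228 | 0.231 | 0.060 | 0.062 |
| 0.25 | 0.228 | 0.227 | 0.053 | 0.056 |
| 0.5 | 0.228 | 0.227 | 0.048 | 0.057 |
| 0.75 | 0.227 | 0.210 | 0.033 | 0.047 |
| 1.0 | 0.227 | 0.203 | 0.029 | 0.052 |

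The Monte Carlo standard error is about 0.004. As a check, type I error ≈ 2[1 − Φ(1.96 × SE/SD)]. At SD 1.0, 1.96 × 0.227/0.203 = 2.19, which gives 0.028 against the simulated 0.029.

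With a true log odds ratio of −0.62:

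| Site SD (log odds) | Mean estimate, planned → with site | Mean SE, planned → with site | Power, planned → with site |
|---|---|---|---|
| 0 | −0.624 → −0.630 | 0.238 → 0.239 | 0.750 → 0.754 |
| 0.5 | −0.601 → −0.639 | 0.237 → 0.242 | 0.730 → 0.752 |
| 0.75 | −0.560 → −0.633 | 0.236 → 0.246 | 0.668 → 0.737 |
| 1.0 | −0.520 → −0.634 | 0.235 → 0.250 | 0.618 → 0.722 |

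Adding site makes the standard error slightly larger. Power rises because the estimate is no longer attenuated: at SD 1.0, estimate/SE goes from 0.520/0.235 = 2.21 to 0.634/0.250 = 2.54.

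**4. Size on the admission-rate scale.** The same two ordered-logit models were fitted with between-authority differences expressed as an SD of the log admission rate (270 patients, 1,200 runs per setting):

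| Assumed SD of log rate | Rate ratio, authorities 1 SD above v. below average | Type I error, planned | Power, planned → with site |
|---|---|---|---|
| 0 | 1 | 0.048 | 0.40 → 0.41 |
| 0.3 | exp(0.6) = 1.8 | 0.040 | 0.36 → 0.39 |
| 0.5 | exp(1.0) = 2.7 | 0.038 | 0.34 → 0.40 |
| 0.7 | exp(1.4) = 4.1 | 0.034 | 0.31 → 0.39 |

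A separate run of 3,000 trials per setting (mean about one admission, rate ratio 0.75) filled in the low end. Power went from 0.402 to 0.404 at SD 0, 0.398 to 0.406 at 0.1, 0.392 to 0.404 at 0.2, and 0.373 to 0.392 at 0.3. Its type I errors at 0.3, 0.5 and 0.7 were 0.044, 0.044 and 0.036. The two sets agree within simulation error: with 1,200 runs, √(0.05 × 0.95/1200) = 0.006 for type I error and √(0.4 × 0.6/1200) = 0.014 for power.

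**The case against.** **The loss may be nothing.** The protocol gives no between-authority variation, and it describes the recruitment areas as alike in one respect: none has specialised outpatient programmes. A log-rate SD of 0.5 or 0.7 implies large regional differences (2.7-fold and 4.1-fold between authorities one SD either side of average). At 0.2 or less, about one point of power is at stake. This objection stands, and the size must be stated as conditional.

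**Omission does not simply widen the interval.** A reader might infer from linear-model reasoning that leaving out authority leaves its variance in the error term and makes the confidence interval too wide, so that adding it would narrow the interval. That does not hold for the planned ordered logistic model: the interval for the log odds ratio becomes slightly wider with site included. What remains is that the planned standard error is somewhat too large for its own, attenuated estimate.

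**The odds ratio changes meaning.** Without site it is averaged over authorities; with site it is conditional on authority. This stands and belongs in the text of the fix.

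**It could be left to the statistical analysis plan.** This does not stand. The protocol itself fixes the a priori covariates and includes one of the two stratification factors.

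**The number of authorities is unclear.** Fraser, Northern, Interior and Vancouver Coastal Health are named, while Vancouver Island Health appears in marked-up text that may be a deletion or an insertion. This stands, so the fix should not set a number.

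**Conclusion.** The mismatch is certain: randomisation is stratified by sex and health authority, and the primary model's fixed covariates include only sex of the two. The direction is also clear. If admissions differ between authorities, the test is mildly conservative, the log odds ratio is attenuated and power is lost.

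The size is conditional on an assumed SD of the log admission rate between authorities. For SDs of 0, 0.3, 0.5 and 0.7, type I error is about 0.05, 0.04, 0.04 and 0.03, and the power loss about 0-1, 2-3, 6 and 8 points. This assumes four authorities, 270 analysed patients and 1:1 allocation.

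A reader might infer that the primary test is invalid, or that the trial is bound to lose power. The documents support neither: false positives are not inflated, and nothing in the protocol shows that authorities differ enough to matter. This is a modest point, worth acting on because the remedy is nearly free and power is already limited.

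**What to change.** In Statistical Analyses, add health authority to the a priori covariates of the primary ordered logistic model, beside group, age and sex. Use as many categories as there are recruiting authorities, and state that the odds ratio is then conditional on site. If authority is deliberately left out, give the reason.

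The cost is one phrase and a few degrees of freedom (three with four authorities, four with five) out of about 270 patients, plus a slightly larger standard error on the log odds ratio. Site is known for every participant at randomisation, so no data collection changes. With no site effect at all, the simulations show no loss of power from including it (0.750 to 0.754, and 0.402 to 0.404). Fixing the term now also avoids a later, data-driven decision on whether to include it.
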